### Patient inclusion criteria

Eligible patients are identified through the registry based on laboratory. To be eligible for inclusion patients have to be adult and diagnosed with diabetes type II according to the recommendations of the Swiss diabetes society which is in accordance to the international diagnostic criteria (Fasting Glucose in blood plasma > 7,0 mmol/l) and a HbA1c > 7.0%. After an initial letter inviting eligible participants to the study the patients are approached during usual care visits for informed consent. All patients will be contacted in consecutive order of appearance in the practice, regardless the reason for the current encounter.

### Patient exclusion criteria

1. Patients who are not able to read and understand the patient information form due to dementia, illiteracy or insufficient German language skills

2. Patients who contacted the practice for emergencies only or as a substitute practice

3. Patients with oncological diseases and/or an estimated life expectancy of less than six months due to severe diseases

### Data collection

Patients will receive detailed written information on the aim of the study. After giving their written informed consent they will receive the questionnaire, containing the SF-36 [33], the PACIC 5A [35,36] and the PHQ-9 [42], and a stamped envelope with the postal address of the university. The patients are asked to return this questionnaire in the envelope to the university. Patients will also be informed that neither the GP nor the practice team has any possibility to get knowledge of their answers. The GP will create a list with the participants and allocate a code to each patient. This code is also marked on the questionnaires. The university only receives the patients' codes and has no access to their names. A second questionnaire is filled out by the GP and the practice nurse for each participant regarding current diagnostic findings (e.g. HbA1c, BD, LDL-cholesterol, weight, pulse etc.), comorbidities, medication, diabetes associated complications, compliance, smoking status and quality indicators for diabetes. This questionnaire is marked as well with the patient's code and will be returned to the university in a stamped envelope.

An independent research assistant of the university will enter the data directly into the SPSS program (version 18.0 or higher). Measurements and analysis will take place before randomization (pre-data-collection) and after 12 months (post-data-collection). Pre-data-collection is estimated to last 3 months (months 2 - 4).

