#### Quality indicators

Quality indicators can be based on process measures or clinical outcome measures. To enable international comparisons, we decided to asses quality indicators for diabetes according to the recommendations of the American Diabetes Association [34]. These quality indicators for diabetes care are also used e.g. by the British National Diabetes Quality Improvement Alliance. The indicators reflect the physical examination (incl. feet) and referrals (incl. eye):

P1: Percentage of patients receiving at least one nephropathy screening per year

P2: Percentage of patients receiving a dilated eye examination or evaluation of retinal photography by an ophthalmologist or optometrist per year

P3: Percentage of patients receiving at least one foot examination per year

P4: Percentage of patients receiving at least one peripheral neurological testing per year

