### Study design

The study is a (prospective) cluster-randomized, open, two-armed intervention study with the GP as the unit of randomization. The design of a cluster randomized study was chosen because this design has optimal internal validity, while avoiding contamination of interventions associated with patient randomization. The flow chart of the study is described in Figure 1.

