### Recruitment of GPs and randomization

The GPs are the unit of randomization. They are eligible for randomization if they participate in the routine primary care of unselected patients to assure that patients of all social levels have unlimited admission to the practice. If they are working in a non-single-handed practice, it is important that they have their own patients which can clearly be allocated to them. From an address database of all GPs in the area of Zurich, St. Gallen and Appenzell every second GP (about 800 GPs in total) was randomly selected, informed about the study and invited to an information meeting by a formal letter of the Department of General Practice and Health Services Research of the University of Zurich at the end of November 2009. Additionally, the project was presented in several quality circle meetings in doctors' networks (regions Zurich, Winterthur, St. Gallen). The aim of the information meeting was to provide the GPs with detailed information on the purpose and the associated effort for participating as well as to give an overview on the course of the whole study. If a GP was not able to attend the meeting but was interested in participation, he was invited to contact the Department of General Practice and Health Services Research and was delivered detailed information about the study by a project assistant.

The GPs who finally agree to participate will be alphabetically ordered in a list with numbers from 1 to 28 (no constraint will be imposed to cluster randomization). With the statistical program SPSS (version 18.0), 14 figures out of 28 will be randomly generated which represent the intervention group. The GPs with the corresponding numbers will be allocated to the randomly generated figures and to the intervention group, respectively. The randomization will be performed by an independent assistant who is not involved in the study and who is blind to the identity of the GPs. GPs will be informed about the group they have been randomized to after the inclusion of patients has been completed to avoid any bias in including patients.

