##### Intervention on the practice nurse

In Switzerland, as in most European countries, the education of practice nurses differs tremendously from the U.S. and it is completely unknown if approaches as in the U.S. can be implemented. The education of practice nurses in Switzerland is less focused on medical issues and addresses mainly administrative matters. Lacking medical knowledge has been identified as an important barrier towards an increased involvement of practice nurse in medical care. Unfortunately, professions as advanced nurse practitioners or physicians' assistants do not or only marginally exist. Therefore, practice nurses represent the only resource for a team approach in primary care. This study challenges the hypothesis that CCM appropriate care can be implemented in primary care. To qualify practice nurses to do so, practice nurses from the intervention group will participate in the well established educational course "Treatment of long term patients - module diabetes" ("Betreuung von Langzeitpatienten - Modul Diabetes"). The course lasts 6 days and will be organized by the union of Swiss practice nurses ("Schweizerischer Verband medizinischer Praxisassistentinnen") [56]. The content of the course is the treatment of diabetes patients (medical basics, diet, practical tips, communication etc.), the role of the practice nurse in a team providing structured care for chronically ills and how to perform a follow-up with the CARAT-monitoring-tool. The tool addresses clinical parameters (e.g. HbA1c, blood pressure, LDL etc.), performed examinations (food control, neurological tests, eye examination etc.) as well as referrals and adherence to the prescribed drugs and other recommendations. The tool contains a traffic-light-scheme, indicating if worsening or improvement has occurred. While giving a quick overlook over the status, the traffic-light-scheme will ease the follow-up for the physician who receives the CARAT-tool after it has been filled out by the practice nurse.

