#### 2. Clinical intervention - Intervention on the patient

The Chronic Care Model has been shown to provide interactions between patients and providers that support optimal patient functional and clinical outcomes [57,58]. Practice nurses were chosen to implement and to deliver the intervention because of the ongoing need for assessment of goal attainment and because of their ability to work with patients to reduce ambivalence to behavior change, collaborate with GPs and reinforce diabetes education. In the European setting, external nurse practitioners do not exist or are not accepted by GPs. In contrast, the practice nurses are already integrated in the primary care setting and have a continuous relationship with study participants including both direct clinical interventions and collaboration with their GP.

The 6 key elements of the CCM will be addressed as follows:

Organization of health care: The specially trained practice nurse will be involved in care. She will monitor the patient during the study with the CARAT-tool. Contacts for monitoring are planned at least every 4 moths but the frequency can be increased according to the clinical situation of the patient. The clinical aim is to assure that standing orders for established clinical practice guidelines regarding frequency of laboratory testing (HbA1c, LDL, nephropathy screening), yearly ophthalmologic exam and performance of foot exam by the nurses facilitates are met.

Clinical information systems: The information on monitoring and appointments with the practice nurse will be collected in the CARAT-monitoring-tool and will be forwarded to the GP based on importance/urgency before the patient encounter to the GP. This way of information transfer between practice nurse and GP is new. This improvement in communication should help the GP to get an immediate overview on the current situation of the patient. It should also help to address current problems - as for instance a detected depression - more accurately. Data entry by the nurses into the registry allows the GP to obtain an overview on self-care goals, clinical parameters over time (BP, HbA1C, LDL, last ophthalmologic exam, aspirin use, foot exam) via a single sheet prior to each patient visit, and provides prompts for issues to be addressed at a given visit.

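### The eye, foot and neurological examination indicators are reported by unblinded practice staff, and only the intervention arm keeps a log of those examinations, so a difference may partly reflect better recording

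*Protocol article*

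**What the plan says.** All references are to the protocol article.

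- **Blinding.** Study design: "The study is a (prospective) cluster-randomized, open, two-armed intervention study with the GP as the unit of randomization". Recruitment of GPs and randomization: "GPs will be informed about the group they have been randomized to after the inclusion of patients has been completed". The baseline form therefore precedes knowledge of the arm; the 12-month form does not.
- **Who reports.** Data collection: "A second questionnaire is filled out by the GP and the practice nurse for each participant regarding current diagnostic findings". The list of contents ends with "compliance, smoking status and quality indicators for diabetes".
- **Independent step described.** Data collection: "An independent research assistant of the university will enter the data directly into the SPSS program". This is data entry; it does not establish whether an examination took place.
- **Outcomes concerned.** Quality indicators lists P1 (nephropathy screening), P2 (eye), P3 (foot) and P4 (peripheral neurological testing), each as a yearly percentage of patients, for example "P3: Percentage of patients receiving at least one foot examination per year". They are secondary outcomes in Table 1, and the Background expects the intervention to improve quality indicators for diabetes care.
- **The log.** Intervention on the practice nurse says that the CARAT tool covers, besides clinical parameters, "performed examinations (food control, neurological tests, eye examination etc.) as well as referrals". I read the word food as foot, in line with the Quality indicators section. The Clinical intervention section has the nurse monitor each patient with the tool: "Contacts for monitoring are planned at least every 4 moths".
- **Controls.** The Abstract states that the control group gets no intervention and usual care.

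**The concern.** Each indicator is the share of patients reported as having had an examination. That share is the true examination rate multiplied by the completeness of reporting. The intervention is meant to raise the first factor. Because its monitoring tool logs these same examinations, it can also raise the second, and in one arm only. The people completing the form know their arm and are themselves the target of the intervention.

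Baseline data cannot correct this, because the change in recording would begin after baseline and be caused by the intervention. Adjustment for age, gender or other patient covariates, as the Analysis section plans, does not reach it either. At stake is the interpretation of P2, P3 and P4: a positive result could not be read as better care without knowing how much of it is better documentation.

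**Working it through.** **Is there a figure in the plan to reproduce?** The plan gives none on recording completeness. Its sample size supplies the group sizes and design effect used below, so I checked that first (Sample size section: difference 0.5, SD 1.2, ICC 0.04, 12 patients per practice, power 80%, alpha 0.05, taken as two-sided).

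- Patients per arm without clustering: 2 × (1.2 × (1.960 + 0.842) / 0.5)² = 90.4, rounded up to 91.
- Design effect: 1 + (12 − 1) × 0.04 = 1.44.
- 91 × 1.44 = 131.04; 131.04 / 12 = 10.92, so 11 practices per arm. 11 / 0.80 = 13.75, so 14 per arm.

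This reproduces the stated 11 and 14 practices, that is, 132 and 168 patients per arm. The primary sample size is not affected by this point.

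**Which outcomes does the log overlap with?**

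| Outcome | Named in the CARAT examination list | Can recording alone shift it? |
|---|---|---|
| P2 eye | yes | yes |
| P3 foot | yes | yes |
| P4 neurological | yes | yes |
| P1 nephropathy | not named (the list ends in etc.) | not shown |
| HbA1c, LDL, blood pressure | listed as clinical parameters | no; logging a value does not change it |
| SF-36, PACIC 5A, PHQ-9 | no | no; patients post these directly to the university |

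**Possible size, using foot examinations.** The Background cites 31.7% of patients without an annual foot examination, so the true rate is set at 1 − 0.317 = 0.683 in both arms. With reporting completeness c_I (intervention) and c_C (control), the spurious difference is 0.683 × (c_I − c_C). The completeness values are assumptions; the documents give none.

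| c_C | c_I | Reported control | Reported intervention | Spurious difference (points) |
|---|---|---|---|---|
| 100% | 100% | 68.3% | 68.3% | 0 |
| 95% | 100% | 64.9% | 68.3% | 3.4 |
| 90% | 100% | 61.5% | 68.3% | 6.8 |
| 80% | 100% | 54.6% | 68.3% | 13.7 |

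**What this could do to a test.** I used a two-proportion normal approximation with effective size N / 1.44 per arm, borrowing the HbA1c ICC of 0.04. The chance of a significant result favouring the intervention is Φ((d − 1.96 × SE₀) / SE₁), where d is the spurious difference and SE₀ and SE₁ are the pooled and unpooled standard errors. For 132 / 168 patients per arm:

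- 95% against 100%: 7% / 8%
- 90% against 100%: 16% / 19%
- 80% against 100%: 48% / 57%

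The nominal value in that direction is 2.5%. Eye examinations (true rate 1 − 0.323 = 0.677) give nearly the same: 7% / 8% in the first case and 47% / 56% in the last.

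**The case against.** The strongest reply has four parts.

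1. **The form is common to both arms and is not the CARAT sheet.** Nothing says that the sheet feeds the form, or what control practices consult when completing it. The article also condenses a fuller protocol, where source-document rules would normally sit. This stands in part: the absence of a source rule is not itself a finding. The point rests on what the article does state, namely who reports, that they know their arm, and that one arm keeps a log of the same events.
2. **The size is assumed.** This stands. The Background figure comes from studies in other settings, and equal recording gives no bias at all. The low proportion of GPs with electronic records, also cited in the Background, does not show that paper notes omit examinations.
3. **The tool is meant to raise real examination rates, so a difference may be genuine.** Also true. As collected, the data do not show how much is genuine, although a check of a sample of practice records could help.
4. **Practice-reported process measures are a pragmatic choice, and only three secondary outcomes are concerned.** This limits the weight of the point but does not remove it.

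A reader might go further and infer that control HbA1c and LDL values could be of any age while intervention values are recent. The documents do not support that: Data collection and Timeframe of the study place the second measurement one year after the first without distinguishing arms, and the four-month interval applies to nurse contacts, not laboratory tests. A reader might also extend the point to the blood-pressure goal or to nephropathy screening. Keeping a log does not lower a reading, and nephropathy screening is not among the examinations that the tool is said to list.

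**Conclusion.** The point holds for P2, P3 and P4 only. In an open trial, unblinded staff report these indicators for their own patients, and the intervention includes a log of the same examinations that controls lack. A difference can therefore partly reflect recording, and independent data entry does not correct that.

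The size cannot be derived from the documents. With a true rate of 68.3% in both arms and complete recording with CARAT, the spurious difference runs from none (equal recording) through 3.4 and 6.8 to 13.7 points (95%, 90% and 80% recording in controls). The false-positive chances rest further on an ICC borrowed from HbA1c. The primary outcome, the sample size and the questionnaires that patients post themselves are outside the point. It is a worthwhile, inexpensive improvement to secondary outcomes, to be made before the 12-month collection.

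**What to change.** Apply one ascertainment rule at 12 months in both arms:

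- **P2, and P1 for consistency:** count the indicator only if a dated eye-specialist report (P2) or laboratory report (P1) from the 12 months is supplied as a copy bearing the patient code.
- **P3 and P4:** require the date of the examination from the practice record in both arms, and do not accept the CARAT sheet as sole evidence.
- **Patient questionnaire:** add two items on foot and neurological examination, using the existing direct mailing to the university. Use them only in a supporting sensitivity analysis, because patients are also unblinded and intervention patients are taught about diabetes.
- **HbA1c and LDL:** attach the dated laboratory report for the 12-month values, as a simple transcription check.
- **Reporting:** describe P2 to P4 as open to differential recording. An intervention nurse may carry CARAT dates into the practice record, so the rule reduces the problem for P3 and P4 without removing it.

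The cost is copying work in the practices and two questionnaire items; no extra assessor is needed. Examinations without documentation will be lost. That loss may not be equal between the arms, so the number of indicators lacking a dated source should be reported by arm.

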### Analysis

We aim to show the reduced level of HbA1c (primary endpoint) in the intervention group using a t-test for independent groups comparison. For binary outcome measures such as success meeting HbA1c, BP and LDL goals, logistic regression will be used to model the relationships between the outcome and treatment group, age and gender. Other potentially important covariates will be identified through exploratory analyses. The longitudinal aspect of the data can be incorporated into the model in various ways, we will utilize the model generalized estimating equations (GEE) approach [52].

For continuous outcomes such as HbA1c levels, blood pressure, lipid levels, SF-36 and the PACIC 5A a repeated measures analysis of variance is appropriate [53]. Fixed effect parameters will include treatment group, age, gender, and other potentially important covariates as the PHQ-9 score.

The primary data analysis will follow the intent-to-treat (ITT) approach where appropriate. This means that all available data from all individuals will be analyzed according to treatment group assignment, regardless of whether or not each individual actually received the assigned treatment.

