### Sample size

Due to its hierarchical structure, sample size calculations for cluster randomized trials differ from sample size calculations for common RCTs [45,46]. The required number of patients increases with the intracluster correlation, estimated in the intracluster correlation coefficient [47]. Based on our previous studies and on data available at the website of the University of Aberdeen [48], we assumed an ICC of 0.04 for the primary outcome. As primary outcome we defined the HbA1c. The sample size calculation was performed with the Cluster Randomization Sample Size Calculator ver.1.02 of the University of Aberdeen.

Unfortunately, no epidemiological data regarding the HbA1c is available from the Swiss primary care setting. Based on previous data and on our inclusion criteria (HbA1c > 7.0%) we assumed a mean HbA1c of 7.7% at pre-data-measurement time and aimed at a reduction in the HbA1c of 0.5% points with the intervention. In accordance to the data from the "Diabetes in Germany" (DIG)-study [49] and the ACCORD trial [50], the SD was assumed to be 1.2. The power was defined as 80%. The significance level was defined to be 0.05. Based on these assumptions and definitions we have to include 12 patients and 11 practices in each arm. In cluster randomized trials a higher drop out rate has to be assumed since the drop out of one cluster leads to the loss of all patients in a cluster. Therefore we assumed a drop out rate of 20%, resulting in 14 practices in each arm and 28 in total [45,46,51].

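### The primary HbA1c test ignores clustering by practice, so at the protocol's own ICC its 5% significance level is really about 10%

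*Protocol article*

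**What the plan says.** The Study design section describes a "cluster-randomized, open, two-armed intervention study with the GP as the unit of randomization". The Sample size section explains that cluster trials need a different calculation, and for HbA1c "we assumed an ICC of 0.04 for the primary outcome". From this it concludes that "we have to include 12 patients and 11 practices in each arm", and adds a 20% dropout allowance, "resulting in 14 practices in each arm and 28 in total". On the error rate: "The significance level was defined to be 0.05".

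The Analysis section gives the primary test: "We aim to show the reduced level of HbA1c (primary endpoint) in the intervention group using a t-test for independent groups comparison". Its intention-to-treat paragraph adds that "all available data from all individuals will be analyzed according to treatment group assignment".

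For binary outcomes, "logistic regression will be used to model the relationships between the outcome and treatment group, age and gender". GEE is then brought in to handle measurements repeated over time. Continuous outcomes, with HbA1c listed again, go to a repeated-measures ANOVA whose listed effects are treatment group, age, gender and covariates such as the PHQ-9 score. The section names no practice effect, cluster-level summary or cluster-robust variance.

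**The concern.** Patients of one GP share a doctor, a team and, in the intervention arm, the same trained nurse. The sample size section accepts that their HbA1c values are correlated, but the primary test assumes that they are not. A test that ignores a positive correlation within randomised clusters uses too small a standard error: it rejects a true null hypothesis too often, and its confidence interval is too narrow.

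At stake is the trial's main claim, because a borderline significant HbA1c result would not be significant at the level the protocol sets. The secondary patient-level models share the omission. The process indicators (eye, foot, kidney and nerve checks) depend on practice habits, so they may cluster more strongly than HbA1c.

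**Working it through.** **Inputs, all from the Sample size section:** difference 0.5 percentage points, SD 1.2, power 80%, alpha 0.05, ICC 0.04, 12 patients per practice, 11 practices per arm before dropout and 14 after. Sidedness is not stated and is settled in step 1.

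**1. Reproduce the planned size.**
- Patients per arm without clustering: 2 × [1.2 × (1.960 + 0.842) / 0.5]² = 90.4, so 91.
- Design effect: 1 + (12 − 1) × 0.04 = 1.44.
- 91 × 1.44 = 131.0 patients; 131.0 / 12 = 10.9, so 11 practices per arm.
- Dropout: 11 / 0.80 = 13.75, so 14 per arm and 28 in total.

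The protocol's figures are reproduced exactly with a two-sided alpha. One-sided, 72 × 1.44 / 12 = 8.6 would give 9 practices, which does not match. The plan therefore takes the variance of the treatment difference to be 44% larger than an independent-patients test assumes.

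**2. True type I error of the patient-level t-test.**
- The standard error is too small by √1.44 = 1.20.
- The effective critical value is 1.960 / 1.20 = 1.633.
- Type I error: 2 × [1 − Φ(1.633)] = 10.2%.
- The nominal 95% interval is 1 − 1/1.20 = 17% too narrow and covers about 90%.
- To hold 5%, the unadjusted p-value would have to fall below 2 × [1 − Φ(1.960 × 1.20)] = 0.019.

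**3. Check by simulation** (100,000 null trials per setting, ICC 0.04, 12 patients per practice).

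| Practices per arm | Patient-level t-test | t-test on practice means |
|---|---|---|
| 11 | 10.2% | 5.0% |
| 14 | 10.4% | 5.1% |

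**4. Sensitivity to the ICC** (formula of step 2, 12 patients per practice).

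| ICC | Design effect | Type I error |
|---|---|---|
| 0.01 | 1.11 | 6.3% |
| 0.02 | 1.22 | 7.6% |
| 0.04 (protocol) | 1.44 | 10.2% |
| 0.06 | 1.66 | 12.8% |
| 0.10 | 2.10 | 17.6% |
| 0.20 | 3.20 | 27% |

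Only 0.04 comes from the protocol. The other values are assumptions; 0.20 illustrates a process indicator that clusters strongly. With 10 analysed patients per practice at ICC 0.04, simulation gives 9.2%.

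**5. Power of a valid practice-level test.**
- 11 per arm: SE = 1.2 × √(2 × 1.44 / 132) = 0.177; noncentrality 0.5 / 0.177 = 2.82. The normal approximation gives 80.5%; the noncentral t with 20 df gives 76.5%.
- 14 per arm: SE = 1.2 × √(2 × 1.44 / 168) = 0.157; noncentrality 3.18; 26 df gives 86.5%.

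**The case against.** The best defence is that the unit of the t-test is not stated. A t-test on practice means is also a comparison of independent groups, and it would be valid. The authors plainly understood clustering when they sized the trial, and the sentence about all individuals defines intention to treat rather than the unit of analysis. This reading is possible, but nothing in the text supports it: no practice-level summary is mentioned anywhere, and the patient-level reading is the natural one. If practice means were intended, the protocol needs to say so.

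It is also fair that the 10% is conditional on an assumed ICC. The size of the inflation depends on it (step 4), but its direction does not: any positive ICC pushes the error above 5%.

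On the secondary models the text is partly silent rather than wrong. The unit for GEE is not defined, and a list of fixed effects does not rule out a random one. ACIC is scored by the practice team and is not a patient-level outcome. This softens the secondary point. Even so, the one reason given for GEE is repetition over time, and grouping on the patient would not correct for practice.

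The second method listed for HbA1c, the repeated-measures ANOVA, does not rescue the primary analysis, because it names no practice term either.

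Finally, the power figures in step 5 refine a sample size that is correct by the method used. They are a minor matter and do not carry the finding. Nor can the point be left to a separate analysis plan: the article names a specific test, and a valid plan would have to depart from it.

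**Conclusion.** The concern holds, and the primary analysis is wrong as written. The design and sample size recognise clustering, but the named test does not, and this roughly doubles the false-positive rate that the protocol sets. An unadjusted p-value between about 0.019 and 0.05 would not be significant once clustering is respected at the assumed ICC. The size of the error rests on three assumptions: the t-test is run on patients, the ICC is near 0.04, and about 12 patients per practice are analysed. This must be corrected, because it affects the confirmatory test of the main hypothesis.

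**What to change.** - **Primary analysis:** replace the t-test with a linear mixed model for HbA1c that has a random practice intercept and Satterthwaite or Kenward-Roger degrees of freedom. A t-test on practice means (26 df if all 28 practices are retained) is a simple alternative. State that this is the one primary analysis of HbA1c and that the repeated-measures model is supportive.
- **Secondary patient-level models:** add a practice random effect, or use GEE clustered on practice with a small-sample variance correction. Say explicitly that practice is the cluster.
- **Power statement:** give about 77% with 11 and 86.5% with 14 practices per arm for the unadjusted practice-level comparison.

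The cost is wording only: design, recruitment and data collection stay as they are. At ICC 0.04 the primary standard error grows by a factor of about 1.20, so p-values and intervals become less favourable but correct. If all 28 practices are retained, power stays above 80%.
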